#### Interim analyses

No interim analyses will be performed. Analyses with measurements before the final data point will be performed only for subsamples or comparisons for which measurements will be completed by then: for example, the quasi-experimental part of the study or the concurrent validation analysis of the EDI-II test results. Therefore, no interim analyses will be used for deciding on study termination.

#### Methods for additional analyses

An analysis of the mediating role of parenting practices between intervention exposure and ECD will be carried out using structural equation models. Parameters will be estimated through weighted least-squares with mean and variance adjustment and the theta parameterization [38].

#### Methods in analysis to handle protocol non-adherence and any statistical methods to handle missing data

Complete case analysis will be performed as well as multiple imputation analysis when appropriate [39]. In regard to adherence, analyses will be complemented with a dose-response analysis.

#### Plans to give access to the full protocol, participant-level data, and statistical code

Full protocol and used code will be shared upon proper and formal request for academic reasons. Datasets are not public so access should be requested formally.

### Oversight and monitoring {21a, 21b, 22, 23}

#### Composition of the coordinating center and trial steering committee

The execution of the trial will be performed by UKA and its research department will function as the coordinating center. The steering committee will be composed of the study investigators and the head of the research department of UKA. The data management team will include IT experts from both UKA and the sponsor institution. At the field, UKA experts will be in charge of electronic data generation through specialized hardware and the InfoKilo v2 information system. IT experts from the National Institute of Public Health of Mexico will monitor data quality and provide advice and recommendations based on auditable algorithms developed for quality control of the data collected.

#### Composition of the data monitoring committee, its role, and reporting structure

The data monitoring committee will be presided by one investigator from the National Institute of Public Health of Mexico who will coordinate with the data management team to review data generating processes and their quality.

#### Adverse event reporting and harms

No unintended adverse effects are expected from the intervention; however, any adverse events related to the execution of the study will be reported to the supervisor in charge of the corresponding area who in turn will immediately report to the IRB.

#### Frequency and plans for auditing trial conduct

The principal investigator will designate appropriately qualified personnel to periodically perform quality assurance checks at mutually convenient times during and after the study and based on auditable algorithms that were developed for quality control of the data collected. These monitoring visits provide the opportunity to evaluate the progress of the study and the adherence to the intervention and obtain information about potential problems. Scheduling monitoring visits will be a function of participant enrollment, site status, and other commitments. The monitor will assure that data are accurate and in agreement with any paper source documentation used, verify that subjects’ consent for study participation has been properly obtained and documented, confirm that research subjects entered into the study meet inclusion and exclusion criteria, and verify that study procedures are being conducted according to the protocol guidelines. If a problem is identified during the visit (i.e., poor communication with the data coordinating center, inadequate or insufficient staff to conduct the study, etc.), the monitor will assist the site in resolving the issues. Some issues may require input from the IRB or of the principal investigators.

#### Plans for communicating important protocol amendments to relevant parties {25}

Protocol amendments will be submitted to the research committee of the National Institute of Public Health Mexico and when necessary and appropriate to the research ethics committee. Authorized changes will be submitted to the Clinical Trials profile of the study.

#### Dissemination plans {31a}

Plans for dissemination include national and international congresses, academic events. and peer-reviewed publications of results at different stages of the project.

## Discussion

We have presented an evaluation design to estimate the effect of a nurturing care intervention on ECD. Most common designs in evaluation are not applicable to estimating effects on ECD given the nature of the outcome. Scales used to assess dimensions of ECD depend on the specific age of subjects; comparing scores across time is problematic since the way in which ECD is measured varies with age. On the other hand, multiple sources of bias should be considered when selecting a design. The main sources of bias are due to confounding factors such as cohort effects, community effects, self-selection, aging effects, and period effects. Community effects can be controlled by randomization. This type of design is known as a cluster randomized trial [40], where the unit that receives the intervention is an aggregate unit, typically subjects are nested into community clusters. Another advantage of the cluster randomized trial design is related to potential spillover effects. For example, in an educational intervention, subjects that receive the intervention may communicate what they learn to neighbors.

Special consideration should be given to the number of communities to be randomized so that intervention effects may be properly separated from community effects. In the extreme case of just two clusters, even with a random allocation, effects from the intervention are totally confounded with the specific characteristics of the two communities. One of the communities may have better outcomes simply because of its own characteristics and not necessarily because of the applied intervention. It has been suggested a total of between ten and fifteen communities per arm [40] to better separate community effects from intervention effects. In the present study, we specified a total of twenty communities per arm.

The stepped-wedge design has been proposed for tackling limitations of classical designs when a control group is not feasible given ethical or logistical considerations [20]. Our design corresponds to a specific stepped-wedge design where effects are assessed as in a parallel design. The main feature of this design is the sequential incorporation of study groups; the defining characteristic of study groups is the time of exposure to an intervention. The assignment of experimental units to study groups is randomized and evaluation can be performed at the same calendar period across study groups; this characteristic precludes effects from time of measurement to be confounded with intervention effects. An alternative version of the stepped-wedge design proposes comparing measurements of the same group before and after intervention; since this occurs in different calendar times, confounding due to period effects cannot be ruled out under this setting [20].

Another type of confounding relates to age; given the nature of ECD outcomes, it is key to compare intervened and not intervened subjects at the same ages. This guarantees that the very same items from ECD scales are used to assess intervention effects. On the other hand, changes in child development at early ages occur very rapidly. This characteristic of ECD complicates using classical estimators such as the difference in differences estimator mainly for three reasons: (1) at the individual level, it is difficult to interpret changes when assessment items vary with age; (2) time differences between measurements across study groups are required to be balanced to avoid confounding; and (3) the distribution of initial ages should also be balanced across study groups. Although these imbalances may be attenuated by using adjustment covariates in models, it would be preferable to avoid these sources of potential bias with a robust design.

Another important source of bias, especially in programs that are not possible to randomize individuals for ethical reasons, is self-selection. Our study has a quasi-experimental component where self-selection is tackled analytically through propensity score matching techniques and difference in difference estimators. The experimental component of our design avoids self-selection bias since all subjects are self-selected to receive the intervention. The key difference between groups is the moment at which intervention is implemented. Groups are incorporated in stages; the last group incorporated is measured before the intervention starts so it serves as a comparison group. Effects are assessed as in a parallel design. In other contexts, the stepped-wedge design has been identified as a quasi-experimental approach; however, it has been noted that a well-conducted stepped-wedge trial where period effects are controlled and participants experience only one condition can in principle be as rigorous as a standard control randomized trial [41].

The intervention proposed share components with other interventions that have proved beneficial effects. Interventions that provide micronutrients for pregnant women and undernourished children have shown improvements in infant nutrition [16, 42, 43]. Also, interventions that include parenting counseling about proper diet and complementary and responsive feeding have showed benefits in the nutritional status of young children [44, 45]. Parent counseling on stimulation has been successful in improving ECD, and this counseling could be made by peers [46], through home visits [47] or workshops and parent sessions [48–51].

Our proposed design has its own limitations that include vulnerability to exogenous shocks that may compromise effects estimation. Although random allocation of communities to the order of intervention implementation balances (in expected value) observed and unobserved characteristics across study groups, benefits of realized interventions could be lower compared to what would be obtained in a situation without an external shock.

Our study design is recommended when the way in which outcomes are measured depends on age, self-selection is present, and assignment is performed at an aggregate level. Although key sources or biases are avoided (e.g., randomization within blocks guarantees that community characteristics that were used to define blocks are balanced between study groups), implementing our design may be challenging given its required sample size and the coordination efforts necessary.

According to our knowledge, this is the first experimental study on ECD in Mexico and the Latin American region which will evaluate a social program designed by a Mexican non-governmental organization, aimed at impacting neurological development through the improvement of child rearing practices. Likewise, this study will allow to generate robust and rigorous information on the causal mechanisms that determine the achievements in neurodevelopment in contexts of high social vulnerability, and this will be useful for the design and implementation of effective ECD interventions.

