**Table 1 Tab1:**
[figure not shown]
Study groups, exposure times, and age of children

The main feature of the proposed design is the possibility of comparing groups of children at the same age range but with a different time of exposure to NPECDP-UKA, at the same calendar period. This design feature will allow to eliminate potential confounding cohort effects since children with the same age across study groups will also share the same year of birth. Table 1 shows the age range of children for each study group at different study calendar periods. The upper age limit of the ECD assessment will be 60 months; therefore, the first group of communities to be exposed to the program will include children aged 1–30 months at their first assessment and these children will be aged 31–60 at their final assessment. At given calendar periods (*t* = 2, 4, 6), the group unexposed to the intervention will function as a control group. For example, the last group of communities to be incorporated to the study (group D) will function as a control group at the last calendar period (*t* = 6). This will allow to estimate the effect of NPECDP-UKA on ECD for exposure times of 30 months (group A vs group D), 24 months (group B vs group D), and 12 months (group C vs group D). Given the rapid changes at early ages and considering the first thousand days of life as a critical opportunity window, we consider that the planned exposure times are adequate to detect changes as well as a gradient of the effect with respect to time exposure. Comparisons between groups will be performed cross-sectionally for children of the same age range. There will be a total of six calendar periods, with a time span of 6 months between the mid-point of consecutive periods and an approximate time span of 6 months between consecutive individual measurements.

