### Outcomes {12}

#### Primary outcome measures

The primary outcomes of the study are the ECD domains assessed through the Child Development Evaluation Test 2nd Edition (CDE-II). The CDE-II, or *Evaluación del Desarrollo Infantil* (EDI-II) in Spanish, was developed and validated in Mexico to screen populations for risk of developmental delays in early childhood. The test has specific items for fourteen age groups of children aged 1–60 months. ECD domains assessed included gross motor, fine motor, language, social, and cognitive skills. The CDE-II is based on age-group specific items, and score results are categorized into three levels following a traffic light interpretation: green (normal development), yellow (developmental lag), and red (at risk of development delay). These three categories will be used as the specific measurement variable, the analysis metric will be the final value (by ECD domain), and the method of aggregation will be the proportion of children falling within each traffic stoplight category. EDI-II will be carried out according to its application guidelines [24, 25], by trained, standardized, and certified research personnel.

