### Sample size {14}

Our main outcome statistic is the proportion of children with developmental lag (yellow category) or at risk of development delay (red category). The effect will be assessed comparing these proportions between the exposed groups and the unexposed group.

Sample sizes were planned so that there are approximately 150 children for each 6-month age interval; this approximates a uniform distribution of observations across age groups and study groups for the relevant age ranges. As mentioned before, given the stepped-wedge design of the study, groups will be incorporated sequentially but comparisons between study groups will be performed at the same study calendar period and for children at the same age interval (see Table 1 for a representation of the stepped-wedge design). Group A will include 1–30-month-old children (*n* = 750); these children will be 31–60 months old at their final measurement and compared to children with the same ages in group D (*n* = 750). This will allow to assess the effect of NPECDP-UKA on ECD after an exposure time of 30 months. Other comparisons are possible. For example, ECD outcomes from group B vs group D (*n* = 900) and group C vs group D (*n* = 1200) at the final study calendar period (Table 1). Table 3 shows the effect size in terms of a difference of proportions given different levels of proportions in the unexposed group (group D), different design effects (DEFF) that consider that measurements in the same community are correlated (DEFF = 1.5, 2.0) [31], a significance level of 0.05 under a bilateral test, and a statistical power of 80.0%.

**Table 3 Tab3:** Sample sizes and effect sizes in terms of a difference of proportions between two groups given a statistical power of 80%

Sample size per group	Proportion in the group without exposure to NPECDP-UKA	Effect size (difference of proportions) given different design effects (DEFF)*		
		DEFF = 1.0	DEFF = 1.5	DEFF = 2.0
750	0.50	0.072	0.088	0.102
900	0.50	0.066	0.081	0.093
1200	0.50	0.057	0.070	0.081
750	0.25	0.065	0.080	0.093
900	0.25	0.059	0.073	0.085
1200	0.25	0.051	0.063	0.073
750	0.125	0.052	0.064	0.075
900	0.125	0.047	0.058	0.068
1200	0.125	0.040	0.050	0.058

*The design effect is a factor that when multiplied by the variance of an estimator under a simple random sampling design corresponds to its variance under a complex sampling design; in this case, a design with clustering of observations within communities

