## Trial status

Recruitment started in July 2019 and was scheduled to end in June 2022. During the first year of the study, once potential participants had been identified, researchers conducted two recruitment phases: the first one from July 15 to December 19, 2019, and the second one from January 21 to February 10, 2020. Due to the COVID-19 public health emergency, recruitment was suspended during early March 2020. Baseline measurements were obtained for a total of 1176 children (764 whose caregivers decided to enroll and 412 whose caregivers decided not to enroll in the NPECDP-UKA).

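### Sharing an age range does not guarantee the same CDE-II items in a pooled contrast; CDE-II age group should be a standing term in the primary analysis

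*Protocol article*

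**What the plan says.** On the instrument, Primary outcome measures states: "The test has specific items for fourteen age groups of children aged 1–60 months". The outcome is the traffic-light category by domain, summarised as a proportion of children.

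On the comparison, Design and setting {9} states: "Comparisons between groups will be performed cross-sectionally for children of the same age range". Sample size {14} adds that "comparisons between study groups will be performed at the same study calendar period and for children at the same age interval", without giving the width of that interval. Table 3 then powers one difference of proportions per contrast, with 750, 900 or 1200 children per group.

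On age balance, Sample size {14} states: "Sample sizes were planned so that there are approximately 150 children for each 6-month age interval", and that "this approximates a uniform distribution of observations across age groups and study groups for the relevant age ranges".

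On analysis, Statistical methods {20a, 20b, 20c} takes the difference of proportions as the effect for binary outcomes. It moves to logistic regression with predictive margins only when observed characteristics turn out unbalanced. It names neither age nor CDE-II age group as a covariate.

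The Discussion concludes, about comparing at the same ages: "This guarantees that the very same items from ECD scales are used to assess intervention effects".

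**The concern.** The guarantee is true of two children of the same age. It is not automatically true of two groups that share an age range several item sets wide. Each group's proportion is then an average over item sets, weighted by how many of its children fall in each. If the weights differ and the proportion of yellow or red results varies with age, part of the difference between groups reflects age mix and not the programme.

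The groups reach their age mix by different routes. Under Table 2, group A at t6 consists of children enrolled at t1 and followed through six measurements, while group D is identified and measured for the first time at t6. An equal mix is therefore something the plan aims for, not something the age limits enforce.

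At stake is whether a property that the article presents as a main strength of the design holds for the primary estimate by construction, or only if enrolment and retention go as planned.

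**Working it through.** **1. The plan's own figures.** For n = 750 per group, control proportion 0.50, difference 0.072 and DEFF 1.0, the pooled proportion is 0.536. With the pooled-variance normal approximation, z = [0.072·√750 − 1.96·√(2·0.536·0.464)] / √(0.50·0.50 + 0.572·0.428) = (1.972 − 1.382) / 0.703 = 0.84, so power is 0.80. All 27 cells of Table 3 reproduce to about 0.0005, using n/DEFF per group and, for control proportions below 0.50, a comparison proportion above control. The sample size arithmetic is not in question.

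**2. Width of each contrast.** Intervals = n / 150; months = intervals × 6, counted back from 60 months.

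| Contrast at t6 | n per group | Intervals | Span | Ages (months) |
|---|---|---|---|---|
| A vs D | 750 | 5 | 30 | 31–60 |
| B vs D | 900 | 6 | 36 | 25–60 |
| C vs D | 1200 | 8 | 48 | 13–60 |

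**3. Item sets pooled.** The average width of a CDE-II age group is 60/14 = 4.3 months. The spans cover 30/4.3 = 7.0, 36/4.3 = 8.4 and 48/4.3 = 11.2 item sets. The article does not give the limits of the fourteen groups, so these counts are averages. Even a six-month interval is wider than the average set.

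**4. How age mix enters.** With weights w for the share of a group's children in item set k, and no programme effect, the pooled difference is Σ(w_Ak − w_Dk)·p_k. This is zero if the weights agree or if p_k does not vary with age. If p changes linearly with age, it equals the gradient per month times the difference in mean age.

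**5. Size.** The documents give no age gradient, so 5 to 15 percentage points per year is assumed.

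- A 1-month difference in mean age shifts the contrast by 5/12 to 15/12 = 0.4 to 1.3 points.
- A 3-month difference shifts it by 1.3 to 3.8 points.
- Table 3's detectable differences are 4.0 to 10.2 points.

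**6. What the planned numbers per interval achieve.** Take ages as uniform and SE of the mean age difference = (width/√12)·√(2·DEFF/n), with DEFF 1 to 2.

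- If 150 per interval is met, only variation within six-month intervals remains. The SE runs from 1.73·√(2/1200) = 0.07 to 1.73·√(4/750) = 0.13 month, worth 0.07·5/12 = 0.03 to 0.13·15/12 = 0.16 point.
- If the numbers per interval are not held, the SE runs from 8.66·√(2/750) = 0.45 to 13.86·√(4/1200) = 0.80 month, worth 0.19 to 1.0 point.

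A chance difference of this kind is sampling error and not bias. Only a systematic difference in who was enrolled or retained would bias the contrast.

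**7. Does the analysis rule close the gap?** Adjustment depends on an imbalance being observed, no criterion is given, and age is not named. It may well be applied to age, but the text does not ensure it.

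**The case against.** The strongest reply is that the Discussion sentence is conditional: children compared at the same age do receive the same items, and both groups meet the same item sets over the range, so only the mix could differ. The traffic-light category is already specific to age, which may flatten any gradient. Age balance is planned in every group, the comparison rule refers to the same age interval, and regression is available if imbalance appears. A separate analysis plan may name age. Most of this stands, and it is why no bias can be claimed. It does not make the guarantee true of a contrast pooled over 30 to 48 months. Nor does reading the interval as six months help, since that leaves about 150 children per group, which Table 3 does not power.

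A reader might go further and infer that the primary contrast is biased or its type I error inflated. The documents do not support that. They report no age breakdown of enrolled children and no change in prevalence with age; the control proportions in Table 3 are planning scenarios, not an age trend. A sizeable imbalance would probably also trigger the planned adjustment.

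A reader might likewise fault the sentence on calendar time, "this characteristic precludes effects from time of measurement to be confounded with intervention effects". In context it contrasts concurrent comparison with before-after comparison, and there it is right. The article gives six months between period mid-points but no period width. The first-year recruitment dates in Trial status concern group A alone, so they show nothing about differences in assessment date between groups.

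**Conclusion.** The point holds as a free improvement, not as a demonstrated error in the design or the sample size. The same-items guarantee is stronger than a pooled range comparison delivers, because each contrast averages over roughly 7 to 11 item sets and equality of mix rests on an approximate recruitment target plus a conditional adjustment that does not name age. If the planned numbers per interval are met in both groups at t6, the effect is negligible: at most about 0.16 point for one standard error of mean age, at the steepest assumed gradient. If they are not met, each month of systematic age difference would be worth about 0.4 to 1.3 points under the assumed gradients of 5 to 15 points per year. The item-set counts assume age groups of average width.

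**What to change.** In Statistical methods, make CDE-II age group a standing stratification or adjustment term in every between-group contrast of the CDE-II outcomes, whether or not imbalance is observed. The article's own tools suffice: logistic regression with age group as a factor, predictive margins standardised to one common age distribution for both groups, and linearised standard errors for clustering. At the planned numbers there are about 150 × 4.3/6 = 107 children per group in an average item set, so the term can be estimated.

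In the Discussion, say that items are the same within a CDE-II age group and that contrasts are standardised for age group. Assessment date within the calendar period may be added as a covariate in a sensitivity analysis.

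The cost is a few lines of text. Age is needed to administer the test, so no new data, visits or children are required. If prevalence does vary with age, the adjustment should also gain some precision, and the choice of primary estimator no longer depends on inspecting the data.
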